**Figure 1. f1:**
[figure not shown]
Flow chart of the BioCer study.

Eligible participants are randomly allocated to the treatment or waitlist groups. The treatment group receives the medical device by postal service, and a treatment period of 12 weeks is initiated on the first day of completing a biofeedback session. Participants in the waitlist group complete daily eDiary entries for 12 weeks from the day of randomization.

Both arms are invited to participate for a 12-week extension period. Participants randomly allocated to the waiting list are offered the possibility of entering a 12-week extension phase with biofeedback treatment. The 12-week extension period is initiated on the first day of the biofeedback training. The participants randomized to the intervention group are invited to a 12-week extension period after completing their 12-week biofeedback treatment, in which they continue with daily eDairy only.

Participants will not have access to the intervention at the end of the study. Beyond the voluntary 12-week extension period, there will be no long-term follow-up on safety and survival status, except in cases of pregnancy.

### Randomization and stratification

Random group allocation occurs a minimum of four weeks after inclusion and after rescreening. If eligible, permuted block randomization is performed. Randomization is stratified on the adjunct use of preventive medication.

### Design of control group

Blinding/masking is not possible owing to the nature of the intervention in question and is thus not performed.

### Recruitment

This trial recruits participants from all over Norway, with inclusion sites covering all health regions. The investigational sites are the neurological departments at St. Olavs Hospital, Trondheim University Hospital, Akershus University Hospital, Haukeland University Hospital, and University Hospital of North Norway. Visits 1 (baseline inclusion) and 2 (rescreening and randomization) are performed by medical doctors with headache expertise. All visits are conducted remotely via video or telephone. Information about the trial and contact information to indicate interest in participation is disseminated through relevant institution webpages and social media platforms. Interested parties may contact the study site directly via email or may be referred. Study personnel are prohibited from enrolling patients for whom they were primarily responsible for treatment and/or follow-up.

### Eligibility criteria

A full list of the inclusion and exclusion criteria is listed in
Table 1. Eligibility is assessed at visits 1 and 2 (
Figure 1), and participants must comply with all inclusion criteria and none of the exclusion criteria to proceed to randomization. Participants are allowed to use one preventive migraine medication if they are stable upon study entry and remain unaltered during study participation. In the case of onabotulinum toxin A injections following the PREEMT injection paradigm, a stable treatment regimen is operationalised as at least three consecutive treatments prior to inclusion. All preventive treatments in use was initiated as part of previous management prior to study entry, and this clinical follow up was continued during trial participation. For other prophylactic treatments, a duration of three months or five half-lives, whichever is longer, of unaltered use is considered stable.

**Table 1. T1:** Eligibility criteria for participation in the BioCer trial.

Inclusion criteria:	Exclusion criteria:
1. 18 years of age or older. 2. Episodic migraines with or without aura diagnosed by a neurologist/physician per International Classification of Headache Disorders 3 ^rd^ edition (ICHD-3). 3. History of at least 4 and up to 14 days of migraines per 28-day period in the 3 months prior to screening (as recalled by the subject). This frequency must be confirmed in the headache diary before randomization to treatment or wait-list control. 4. At least three months of experience with smartphone and access to an iOS or Android phone at home. 5. Capable of giving signed informed consent with includes compliance with the requirements and restrictions listed in the informed consent form (ICF) and in this protocol. 6. Onset of migraine before age 50 years.	7. More than 14 days of headache (all types) per 28-day period. 8. Subjects diagnosed with trigeminal autonomic cephalalgias and neuralgias. 9. Subjects with secondary headache conditions. 10. Subjects with pathologies that inhibit use of the device according to the instructions for use (e.g. blindness, deafness). 11. Use of non-pharmacological preventive treatment (meditation, physical therapy, psychotherapy as a headache treatment, acupuncture etc.) with the exception of stable treatment for other indications than migraine. 12. Use of concurrent migraine preventive medication, with the exception of stable dose ( ≥ 3 months) monotherapy of migraine preventive medication. 13. Subjects taking opioids ( ≥ 3 days per month) or barbiturates at the time of screening. 14. Subject participates in another clinical investigation or has participated in CER-MIG-1. 15. Alcohol overuse or illicit drug use. 16. Subject who is unlikely to follow Clinical Investigation Plan or where treatment seems futile in the opinion of the investigator or have demonstrated an inability to sufficiently adhere to headache diary entries (<70%).

### Ethics

This study is conducted in accordance with the principles of ISO 14155:2020 (Clinical Investigation of Medical Devices in Human Subjects), Good Clinical practice, and the Guidelines of the International Headache Society. The study is approved by the Regional Committees for Medical Research Ethics (REK, approval number 502734. Date of approval 2022-10-14) and the Norwegian Medical Product Agency (NOMA) (reference number 22/17254-5. Date of approval 2022-09-01) prior to initiation. Substantial protocol amendments will be reviewed by competent authorities before implementation. Data protection follows the GDPR. We adhere to the Declaration of Helsinki.

To ensure that all subjects have similar opportunities to benefit from enrolment, participants randomized to the waitlist group are offered treatment following the conclusion of the waitlist period. Consent is collected by the investigator conducting the screening visit. Study information is sent in advance of visit 1 by email, scripted study information is provided orally, and any questions are addressed during visit 1 prior to signing to ensure that consent is obtained in all cases. Consent is collected by a digital signature via a national electronic data entry application («Helsenorge»). Study personnel are prohibited from recruiting patients for whom they are directly responsible for treatment.

### Study intervention

Investigational medical device

The medical device Cerebri consists of a smartphone app and a set of two wireless non-invasive sensors. Both sensors are skin-contact-dependent. One sensor is attached to the index finger and measures HRV and peripheral skin temperature. The second sensor is attached to the skin over the upper trapezius muscle fibers using adhesive electrodes and measures muscle tension as surface electromyographic voltage (
Figure 2A and
2B). The sensors transmit the measurements to the user’s smartphone by Bluetooth technology and display them in real time to the user. Participants receive the sensors by mail together with a brief written onboarding guide. All training is delivered in a standardised, app-based format without individualised or therapist-led instruction. The app guides users through the first three biofeedback sessions, and provides a library with textual instructions on exercises that the user can choose to use in their biofeedback training. By following instructions for suggested exercises displayed in the Cerebri smartphone app, the subject trains on influencing the measured parameters in the desired direction during each biofeedback session.
Figure 3A-C illustrate how visualization of the physiological measures is displayed on their smartphone. Exercises to facilitate successful manipulation of the physiological parameters include breathing techniques, progressive muscle relaxation, and awareness training. A visual breathing pacer to support paced breathing is available in the mobile app to the user during the entire treatment session. It is desirable to increase HRV and peripheral skin temperature and lower neck muscle tension. Participants are instructed to sit comfortably in a quiet room during treatment. Throughout the intervention period, participants are required to complete a 10-minute biofeedback session at least once daily at a time of their choosing. They have the option to perform as many as six sessions each day.

**Figure 2. f2:**
[figure not shown]
A, B: The investigational medical device Cerebri finger sensor and EMG sensor.

**Figure 3. f3:**
[figure not shown]
Screen shots of the biofeedback treatment in the Cerebri mobile application, showing the HRV (A), EMG (B) and temperature (C) modality interface.

### Data collection

eDiary and biofeedback

Data on headache is collected prospectively as a patient-reported outcome measure in an eDiary integrated into the Cerebri smartphone app. Daily entries are encouraged, but the app allows the entry of registrations from the two previous calendar days. The app includes daily reminders to promote adherence. The tool is designed such that when participants report headaches, they are prompted to answer additional questions. Data collected in the diary include the estimated duration of headache, intensity of headache using an 11-point scale (0-10), and the use (type, dose, and number of administrations) of acute medications (triptan, paracetamol, NSAIDs, opioids, other), and information on whether acute medications relieved headache (
Table 2 and
Figure 4A and
4B). Participants are followed up with telephone calls at week 2, week 4 and week 8 to promote adherence (
Figure 1).

**Table 2. T2:** Overview of the eDiary variables used for the mobile application.

Variable	Data input
Headache	Yes/No
Headache recognized as migraine	Yes/No
Intensity of headache	1-10
Duration of headache	0.5 to 24 hours
Acute medication	Yes/No
Type of medication	Medication name and dosage
Did the acute medication alleviate the headache	Yes/No
Menstruation	Yes/No

**Figure 4. f4:**
[figure not shown]
A and B: Screen shots of the eDiary in the Cerebri mobile application.

A web-based dashboard solution enables study personnel to access a real-time overview of adherence to eDiary and biofeedback treatment. Thus, study personnel can identify and reach out to participants with low adherence. In the case of technical issues, a support service provided by the sponsor is available. The dashboard also includes information regarding the migraine/headache status on a given day and acute medication use. This information will be accessible to study personnel in the baseline period for rescreening purposes. Post randomization, only the adherence data is available.

Questionnaires

Subjects are asked to complete validated questionnaires at the end of each 28-day period to measure the headache-related impact on the quality of life and their impression of treatment efficacy. The questionnaires used in this trial are the Migraine-Specific Quality-of-Life Questionnaire (MSQ) v2.1
^
13
^ and the Patient Global Impression of Change (PGI-C).
^
14
^ The MSQ is copyrighted and registered with the United States Library of Congress by Glaxo Wellcome, Inc. A written permission for use is obtained prior to use.

Electronic patient record

Patient records are the source of information regarding medical history, current medications in use, and previous trials of prophylactic migraine treatment acquired during visit 1. Alterations in health status, including treatment-emergent adverse events during trial participation are registered in the medical records.

Study-specific electronic case report form (eCRF)

An eCRF applying the WebCRF3 software (version 3) (
https://webcrf3.medisin.ntnu.no) was developed for this study. The webCRF software is provided and maintained by the Unit for Applied Clinical Research (AKF) at the Faculty of Medicine and Health Sciences, NTNU. Data collected during study visits, telephone consultations, and safety information are entered. Data are stored in a pseudo-anonymous manner, and each study participant is identified using a unique study identification (ID) number. An open-source alternative OpenClinica (
https://www.openclinica.com/get-free-community-edition-software) is able to perform an equivalent function as WebCRF3.

Study monitoring

No data-monitoring committee is appointed for this study. An independent Data Monitor will be used for review of the study in accordance with a Monitoring Plan.

Data management

Data management is guided by the data management plan. Data validation and verification of a minimum of 10% of participants will be conducted before data lock. Data lock can be performed when the last participant ends its 12 week post-randomization period, that is, while the participants are still in an extension period.

### Statistical analysis

Research hypothesis

The primary endpoint is to investigate the change in the mean number of migraine days from baseline to the last 28-day period in the treatment group compared with the wait-list control group. Thus, the null hypothesis (H0) and alternative hypothesis (H1) to be tested in relation to the primary objective are as follows.
•H0: The change in the mean number of migraine days from the 28-day baseline to the last 28-day period in the treatment group is equal to the change in the mean number of migraine days from baseline to the last 28-day period in the wait-list control group.

vs.
•H1: The change in the mean number of migraine days from the 28-day baseline to the last 28-day period in the treatment group is not equal to the change in the mean number of migraine days from baseline to the last 28-day period in the wait-list control group.

Sample size

The sample size calculation is based on an assumption of the effect size derived from a relevant meta-analysis of the efficacy of biofeedback in treating migraine
^
15
^ and a randomized pilot study.
^
9
^ Provided an effect size of d = 0.4, a significance level alpha of 0.05 (two-sided), power 0.8, and a dropout rate of 30% in the post-randomization period, the required sample size of this study was estimated to 286 participants. The anticipation of high dropout rates in this study is justified in the significant challenge of maintaining participant adherence observed in home-based mHealth studies.
^
9
^
^,^
^
16
^

Protocol deviations

Participants with incomplete or missing headache diary entries in more than 30% of days in the post-randomization period, participants with more than 30% missing or incomplete biofeedback sessions in the treatment arm, and participants initiating new or altering the use of their established preventive headache medications during the trial, are considered protocol deviators.

Statistical analysis plan

The statistical analysis plan (SAP) will include a technical and detailed description of statistical analysis. Statistical analyses will be conducted by an independent statistician. The analysis will follow a predefined order, where the primary efficacy endpoint is analyzed first. The trial statistician will analyze the efficacy outcomes without knowledge of treatment allocation by using a dataset with study arm allocation coded as groups A and B.

Data analysis set

For the efficacy analysis, the full analysis set includes all randomized participants and constitutes the intention-to-treat (ITT) population. The per protocol (PP) population includes all randomized participants without protocol deviations.

Analysis dataset 1 is defined as the data from the 16-week period for all randomized participants and does not include extension period data. The 12-week post-randomization period in the biofeedback arm starts on the date of the first biofeedback session. Data lock for the evaluation of efficacy endpoints can be performed upon the completion of this dataset.

The safety data set includes all participants exposed to the biofeedback device.

Primary endpoint analysis

Analysis of the study endpoints will be performed in the ITT (all randomized subjects) and PP populations.

The primary endpoint variable is migraine days. The operational definition used for the analysis will be prespecified in the SAP.

The planned analysis strategy involves a mixed logistic regression model which will include all available daily eDiary entries. The mixed logistic regression model will be used to estimate the difference in the change from baseline in the mean number of migraine days per 28-day period between the treatment and waitlist groups. The model will include the presence or absence of migraine on each day from the baseline and 12-weeks post randomization periods as a dependent binary variable, treatment allocation, time period (baseline, week 1-4, week 5-8 and week 9-12) and an interaction term between treatment allocation and post-randomisation time-periods are included as categorical fixed effects, together with the stratification variable (concomitant preventive medication use). The patient ID will be included as a random effect. The site of inclusion will also be assessed as a potential random effect prior to the unblinding of the statistician to the treatment allocation. The model does not require explicit imputation, as mixed models yield unbiased estimates under the assumption that data are missing at random. This assumption will be assessed and sensitivity analyses considered if warranted.

The primary effect estimate will be the model-based estimates of the difference in change from baseline in mean monthly migraine days between the treatment and waitlist groups, presented with a 95% confidence interval.

Baseline variables that are considered to be highly predictive of outcomes will be discussed and identified
*a priori* and described in the SAP. These variables will be included in multivariate analysis. The SAP will also detail the analysis strategies for the secondary outcomes. Post hoc stratified analyses by sex (women vs. men) and assessment of sex interaction will be conducted.

The statistical analysis plan includes predefined sensitivity analyses, restricting the primary analysis to the per-protocol set and, if feasible, subgroup analyses according to adherence status. Specifically:
•Participants in the interventional group with >90% biofeedback adherence in all three 28-day periods will be compared with the remaining participants in the interventional arm with lower adherence.•Participants in the interventional group with >90% adherence during weeks 1–4 will be compared with the remaining participants in the interventional arm with lower adherence in that same period.

Safety data

Safety objectives will be assessed by collecting data on treatment-emergent adverse events encountered during biofeedback training, including adverse events (AEs), serious adverse events (SAEs), adverse device effects (ADEs), serious adverse device effects (SADEs), and unanticipated SADEs (USADEs), and by evaluating the frequency and severity of these occurrences.

All data on treatment-emergent adverse events, ADEs, SADEs, and USADEs will be categorized and summarized. The frequency and severity of treatment-emergent AEs, ADEs, SADEs, and USADEs will be summarized for all enrolled participants and the entire duration of the intervention. Adverse events occurring more than once in individual participants will also be summarized and presented descriptively.

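### The 12-week outcome clock starts at the first session in the biofeedback arm but at randomization on the waitlist, so a never-starter has no days in the primary contrast

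*Protocol article*

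**What the plan says.** The protocol article sets time zero separately for each arm.

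- Biofeedback arm, Study design (text under Figure 1): the device is mailed to participants after allocation. On the clock, that section states: "a treatment period of 12 weeks is initiated on the first day of completing a biofeedback session". The data analysis set paragraph under Statistical analysis carries this into the analysis: "The 12-week post-randomization period in the biofeedback arm starts on the date of the first biofeedback session".
- Waitlist arm, Study design: "Participants in the waitlist group complete daily eDiary entries for 12 weeks from the day of randomization".
- Analysis population, Statistical analysis: "the full analysis set includes all randomized participants and constitutes the intention-to-treat (ITT) population".
- Primary model, Statistical analysis: "The model will include the presence or absence of migraine on each day from the baseline and 12-weeks post randomization periods". The same paragraph says that every available diary entry is to be used.
- Missing data: no imputation, on the ground that "mixed models yield unbiased estimates under the assumption that data are missing at random".
- Data management: the lock may take place once the last participant has finished the 12-week period after randomization.

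No latest date for a first session is given, and no substitute start date for someone who never has one.

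**The concern.** In one arm the clock starts with something the participant does after randomization; in the other it starts with randomization itself. Three consequences follow from the text.

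1. A biofeedback participant who never completes a session has no start date, and therefore no post-randomization days of any period. That person counts in the ITT set but barely informs the comparison that the ITT analysis is meant to make. Not starting is possible in one arm only, and it may well go with low engagement.
2. Diary days between randomization and first session are unassigned in the biofeedback arm, while the same days after randomization are week 1 onward on the waitlist. The two week 9-12 windows are therefore offset by the start delay.
3. The data-lock rule has no end date for a never-starter.

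At stake is whether the primary estimate compares the arms as randomized. The missing-at-random statement does not settle this, because the days may have been recorded and simply have no place in the model. The per-protocol analysis would not show the problem either: a never-starter misses more than 30% of sessions and is excluded there.

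**Working it through.** **The plan's own figure.** Sample size inputs (Statistical analysis, Sample size): d = 0.4, two-sided alpha 0.05, power 0.80, 30% dropout. Allocation is not stated; 1:1 is assumed. A two-sample t-test needs 100 per arm, and 200/0.7 = 286, the stated total. (The normal approximation gives 99 per arm and 198/0.7 = 283.) The figure reproduces, and the time origin does not alter it. It gives 286/2 = 143 randomized per arm for what follows.

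**Offset of the primary window.** With start delay D days (not in the document), biofeedback weeks 9-12 are days 57+D to 84+D after randomization, against days 57-84 on the waitlist. The overlap is 28 - D days.

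| Assumed D | Biofeedback weeks 9-12 | Days shared with waitlist |
|---|---|---|
| 3 | 60-87 | 25 |
| 7 | 64-91 | 21 |
| 14 | 71-98 | 14 |
| 28 | 85-112 | 0 |

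**What the offset could do with no treatment effect.** Assume that migraine days per 28 days drift down in both arms by A(1 - exp(-t/T)), with A = 1 to 2 days and T = 28 to 56 days. Let m be the mean of exp(-t/T) over days 1-28: 0.621 for T = 28 and 0.780 for T = 56. The apparent benefit in period k (1, 2, 3) is

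A × (1 - exp(-D/T)) × m × exp(-28(k-1)/T).

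For example, with A = 1, D = 7, T = 28, k = 1: 0.221 × 0.621 = 0.137. For k = 3 this is multiplied by exp(-2) = 0.135, giving 0.019.

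| Period | T = 28: A = 1, D = 7 to A = 2, D = 14 | T = 56: A = 1, D = 7 to A = 2, D = 14 |
|---|---|---|
| Weeks 1-4 | 0.137 to 0.489 | 0.092 to 0.345 |
| Weeks 5-8 | 0.051 to 0.180 | 0.056 to 0.209 |
| Weeks 9-12 | 0.019 to 0.066 | 0.034 to 0.127 |

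The shift is small in the primary period and larger in the two earlier periods, which are key secondary endpoints.

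**Never-starters.** At assumed rates of 5% and 10%, 143 × 0.05 = 7 and 143 × 0.10 = 14 people have no post-randomization day. If their true change is 2 days worse than that of starters (assumed), leaving them out moves the arm mean by 0.05 × 2 = 0.1 to 0.10 × 2 = 0.2 days.

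**Scale.** The protocol gives no SD. At an assumed SD of change of 3.5-4.5 days, d = 0.4 is 1.4-1.8 days. The never-starter shift is then 0.1/1.8 = 6% to 0.2/1.4 = 14% of the targeted effect.

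**The case against.** The best defence is that the clock follows the objective. The trial studies 12 weeks of daily use, and the endpoint is the last 28 days of the treatment phase. With a posted device, a clock from randomization counts days on which treatment is impossible. The protocol also defers technical detail to an SAP that is not shown, says that the missing-at-random assumption will be assessed, and lets staff contact participants with low adherence. This supports keeping the first-session clock somewhere in the analysis. It does not remove the conflict: the start rule is stated here, not left open, and it sits beside an ITT set of everyone randomized.

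Several stronger conclusions are tempting, but the document does not support them.

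- *Never-starters are excluded from the ITT set.* They are not. They remain in it and their baseline days can enter the model; what they lack is post-randomization days.
- *Every waitlist participant contributes outcome data.* The 30% dropout allowance is not confined to one arm. Every waitlist participant has a defined window, which is a weaker statement.
- *People start on a migraine-free day, which biases the result.* Nothing says so. Even if granted, with a lag-1 correlation of up to 0.333 the influence on day 57 is of order 0.333 to the power 56, effectively zero. It could touch weeks 1-4 but not the primary period.
- *The masking of the statistician fails.* The protocol promises analysis "without knowledge of treatment allocation by using a dataset with study arm allocation coded as groups A and B". A file organized by study day or period need not hold randomization or first-session dates, so a failure is not shown.

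**Conclusion.** The point holds as a conflict between a stated rule and the stated analysis population. The arms have different time origins, nothing reconciles them, and a biofeedback participant who never starts contributes essentially nothing to the week 9-12 contrast. The reason to correct it is this conflict, not a demonstrated large bias.

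On size, the effect on the primary endpoint is probably modest: about 0.02-0.13 days from a 7-14 day delay and 0.1-0.2 days from 5-10% never-starters, both in favour of biofeedback. Delay, drift, never-starter rate and the 2-day difference are all assumptions; the document gives none of them, so the actual bias cannot be computed. Weeks 1-4 (0.09-0.49 days) and weeks 5-8 (0.05-0.21 days) are more exposed to the delay under the same assumptions.

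**What to change.** For the ITT efficacy analyses:

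1. Take the randomization date as day 1 in both arms, with periods of days 1-28, 29-56 and 57-84.
2. Include all diary days in those periods for all randomized participants, whether or not they ever complete a session.
3. State that biofeedback-arm participants keep the diary between randomization and first session; the protocol does not say so now.
4. Tie the data lock for these analyses to day 84 after the last randomization, so that it has an end date for everyone.
5. Keep the first-session clock as a supplementary analysis, labelled as conditional on starting.

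This concerns analysis windows only and leaves the treatment period as it is.

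The cost is a reworded paragraph and re-windowing of diary data, provided that entries exist for the gap days. There is some dilution. With a one-week delay, days 57-84 are about treatment weeks 8-11. Never-starters kept in with no effect would also dilute d = 0.4 to 0.4 × 0.95 = 0.38 at 5% or 0.4 × 0.90 = 0.36 at 10%, and power at 100 per arm would fall from 0.81 to 0.77 or 0.72. That is the effect of assignment, which an ITT analysis is meant to estimate.

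Adding one fixed postal lag to both arms is not a good substitute. It needs waitlist diary days after day 84, which may be absent or fall in the extension, when waitlist participants may be using the device.

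### The primary model as written gives each arm its own baseline level although baseline precedes randomisation, so the effect estimate is valid but less precise than it could be

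*Protocol article*

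**What the plan says.** In the Protocol article, Statistical analysis section, under Primary endpoint analysis, the dependent variable is daily migraine status, with the baseline days included alongside the 12 post-randomisation weeks. The categorical fixed effects are "treatment allocation, time period (baseline, week 1-4, week 5-8 and week 9-12) and an interaction term between treatment allocation and post-randomisation time-periods", plus the stratification variable. Patient is a random effect, and site is to be considered as one. The result to be reported is fixed as well: "The primary effect estimate will be the model-based estimates of the difference in change from baseline in mean monthly migraine days", treatment against waitlist, with a 95% confidence interval.

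Under Randomization and stratification the order of events is clear: "Random group allocation occurs a minimum of four weeks after inclusion and after rescreening". The baseline diary is therefore complete before any participant has an arm.

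The Sample size paragraph assumes a standardised effect of 0.4, tests at the two-sided 5% level with 80% power, allows for 30% loss after randomisation, and concludes that "the required sample size of this study was estimated to 286 participants". It does not say whether d is standardised on the SD of the 28-day count or on the SD of its change. No baseline-to-follow-up correlation is given anywhere.

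**The concern.** With baseline as the reference period, a treatment term that stands beside the treatment by post-randomisation-period terms has one meaning: the arm difference before treatment. The two arms and four periods form eight cells, and the listed terms fit all eight freely. Each arm thus gets its own baseline level. Randomisation after baseline makes the true difference between those levels zero, so the model spends information on estimating a known quantity. The weeks 9-12 effect then becomes the later arm difference minus the whole observed baseline difference.

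What is at stake is precision. A model with one common baseline level subtracts only the part of the baseline imbalance that predicts the later difference. Its confidence interval is narrower from the same data.

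**Working it through.** **1. The plan's own figure.** Inputs from the Sample size paragraph: d = 0.4, two-sided alpha 0.05, power 0.80, dropout 30%. The article states no allocation ratio, so 1:1 is assumed. A two-sample t-test needs 100 per arm, 200 in total, and 200 / (1 − 0.30) = 285.7, hence 286. The stated number reproduces exactly. (The normal approximation gives 99 per arm, and 198 / 0.70 rounds up to 283.)

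**2. Variance of the two contrasts, equal variances.** Assume a linear analogue with a patient random intercept, complete data, and correlation ρ between the baseline and weeks 9-12 counts. In units common to both:

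- arm-specific baselines (difference in differences): 2(1 − ρ)
- common baseline: 1 − ρ²
- share of variance removed: 1 − (1 − ρ²) / [2(1 − ρ)] = (1 − ρ) / 2

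| ρ (assumed) | Share removed |
|---|---|
| 0.4 | 30% |
| 0.5 | 25% |
| 0.6 | 20% |
| 0.7 | 15% |
| 0.8 | 10% |
| 0.9 | 5% |

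**3. Effect of the entry rule.** Table 1 requires 4 to 14 migraine days per 28, confirmed in the diary, so the baseline SD is likely to be smaller than the follow-up SD. With k = baseline SD / follow-up SD, the change contrast has variance proportional to 1 + k² − 2kρ and the baseline-adjusted contrast to 1 − ρ². The share removed is (k − ρ)² / (1 + k² − 2kρ), which equals (1 − ρ)/2 at k = 1. Illustrative values:

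- k = 0.87, ρ = 0.28: 0.3481 / 1.2697 = 27%
- k = 0.67, ρ = 0.28: 0.1521 / 1.0737 = 14%
- k = 0.87, ρ = 0.58: 0.0841 / 0.7477 = 11%
- k = 0.67, ρ = 0.58: 0.0081 / 0.6717 = 1%

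The restriction lowers both ρ and k. These pull in opposite directions, and the loss vanishes as ρ approaches k.

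**4. Simulation checks, 100 per arm.** All settings are assumed; none comes from the documents.

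| Check | Contrast | Variance removed |
|---|---|---|
| Random-intercept logistic, no entry restriction, ρ about 0.45 / 0.64 / 0.77 | log-odds, weeks 9-12, main effect dropped | 25% / 16% / 12% (model-based) |
| Random-intercept logistic, baseline 4-14 days, 150 replicates per setting | weeks 9-12, main effect dropped | about 4-17% |
| Same data | days, baseline adjustment against change | about 8-20% |
| 28-day counts, baseline 4-14 days, 3,000 replicates, seven settings, ρ 0.28-0.58, k 0.67-0.87 | days, baseline adjustment against change | 6-25% |

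In the first row the model-based variances were 0.00856 against 0.00644, 0.00860 against 0.00719, and 0.00870 against 0.00766. With only 60 data sets per setting, the empirical variances moved in the same direction but are too noisy to size the gain. In the runs with the entry restriction the estimators were unbiased under the null.

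**5. What this means for power.** The answer depends on which SD standardises d. With 100 evaluable per arm and equal variances:

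- d on the SD of change: the planned 80% already applies to the difference in differences. A common baseline multiplies the SD by √((1 + ρ)/2), which raises power to about 0.90 at ρ = 0.5, 0.885 at 0.6 and 0.85 at 0.8.
- d on the SD of the count: the difference in differences has power of about 0.73, 0.81 and 0.885 at ρ = 0.4, 0.5 and 0.6. The common-baseline contrast has 0.87, 0.90 and 0.94.

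The direction is the same under both readings. The level of power cannot be fixed from the documents.

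**The case against.** The strongest reply is that nothing is misstated. The endpoint and H0 are defined as a between-arm difference in change from baseline, and the listed model estimates that. This stands: the point concerns efficiency and not validity.

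A second reply is that limiting the interaction to the post-randomisation periods is how a common-baseline model is usually described, and that the article leaves technical detail to the SAP. This stands in part. The authors may intend the better model, but that model would not also list treatment allocation as a term of its own, and an SAP that follows the article would inherit the loss. Prognostic covariates named later would not remove it while baseline days stay in the outcome with an arm-specific level.

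A third reply is that the algebra is exact only for a linear model with complete data, whereas the planned contrast is likelihood-based on the log-odds scale and then converted to days. This is correct, and it is why the logistic fits are shown. They agree in direction and give a similar or smaller gain.

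A reader might also infer that chance baseline imbalance makes the log-odds null differ from the stated H0 in days. It does not. Hypotheses concern population values. With equal true baselines, a zero weeks 9-12 interaction and an equal change in days coincide under the model.

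**Conclusion.** The primary model, as the article lists its terms, estimates a baseline difference that randomisation has already set to zero. The effect estimate is valid and type I error is unaffected by this choice, but its variance is higher than needed. A reasonable working range for the avoidable part is 5-30% of the variance. That range rests on assumed correlations and on the assumed effect of the 4-14 day restriction. It is not a bound: the loss is smaller still where the correlation comes close to the ratio of the SDs. No single percentage can be drawn from the documents.

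A reader might conclude that the trial is underpowered or that its estimate is biased. The documents support neither. The 286 reproduces, and if d is on the SD of change, the planned 80% already refers to this contrast, so the remedy is pure gain. The point is a free improvement and not an error that threatens the trial's conclusion.

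**What to change.** Drop the treatment main effect from the primary model. Keep the four-level period, the three treatment by post-randomisation-period terms, the stratification variable and the patient random effect. Both arms then share one baseline level, and the weeks 9-12 term carries the primary comparison. If this is already the intention, one sentence in the SAP saying that the baseline level is common to both arms settles it.

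An alternative is to model the post-randomisation days only, with each patient's baseline migraine-day rate as a covariate. It also uses baseline efficiently, but it is not equivalent: in a logistic model the two condition on different things, and their odds ratios are not interchangeable. One should be chosen and named before the statistician is unblinded.

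The cost is one model term in the protocol and SAP. It needs no new data and no more participants, and it introduces no bias under randomisation.
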